#### Sample size calculation

2.2.2

Sample size determination used non-inferiority framework with utilization rate as primary outcome. Based on 70% utilization in clinic-based programs (historical controls) and 5% non-inferiority margin, 18 participants per site (*n* = 54 total) provides 80% power at *α* = 0.10 (one-sided). This sample accounts for an anticipated 15% dropout rate (approximately 8 participants), yielding a minimum evaluable sample of 46 participants. Dropout is defined as withdrawal of consent, loss to follow-up, or inability to complete ≥50% of the home-RAT phase. Sensitivity analyses will compare intention-to-treat (all enrolled) and per-protocol (≥75% session completion) populations.

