### Statistical analysis plan

2.7

The primary analysis evaluates non-inferiority of the observed utilization rate against a 70% historical benchmark derived from clinic-based RAT programs, with a pre-specified non-inferiority margin of 5%. Non-inferiority is demonstrated if the lower bound of the one-sided 95% confidence interval for the observed utilization rate exceeds 65%. This analysis follows intention-to-treat principles, including all enrolled participants regardless of completion status; participants who withdraw are assigned zero utilization for remaining sessions.

For secondary clinical outcomes (FMA-UE, ARAT, grip strength, EQ-5D-5L, SIS-16, PROMIS-10), linear mixed-effects models are employed with fixed effects for time (categorical: baseline, Week 6, Week 8, Week 12, Week 24), site, and baseline severity (FMA-UE score), and a random intercept for participant to account for within-subject correlation across repeated measures. An unstructured covariance matrix is specified, with model fit compared against compound symmetry using the Akaike Information Criterion. The assumption of normally distributed residuals will be assessed using Q-Q plots and the Shapiro–Wilk test; non-normal outcomes will be analysed using generalized linear mixed models with appropriate link functions. Multiple comparisons across secondary outcomes are controlled using the Benjamini-Hochberg False Discovery Rate procedure at q = 0.05.

Exploratory subgroup analyses examine treatment effect heterogeneity by stroke chronicity (<6 months vs. ≥6 months), baseline severity (FMA-UE < 30 vs. ≥30), age (<65 vs. ≥65 years), and cognitive status (MoCA 21–25 vs. >25) using interaction terms in the mixed models. These are hypothesis-generating and interpreted cautiously given the sample size.

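### Section 2.2.2 removes the expected 15% dropout from the sample, but the section 2.7 primary analysis keeps all 54 and zero-fills after withdrawal; attrition during home training therefore lowers the tested rate, and neither the 70% nor the 80% power is adjusted for it

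*Protocol article*

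**What the plan says.** Section 2.2.2 (Sample size calculation) starts from a clinic figure: "Based on 70% utilization in clinic-based programs (historical controls) and 5% non-inferiority margin". The power claim is "18 participants per site (*n* = 54 total) provides 80% power at *α* = 0.10 (one-sided". Attrition is then handled by taking people out: "This sample accounts for an anticipated 15% dropout rate (approximately 8 participants), yielding a minimum evaluable sample of 46 participants". The definition of attrition is wide: "Dropout is defined as withdrawal of consent, loss to follow-up, or inability to complete ≥50% of the home-RAT phase".

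Section 2.7 (Statistical analysis plan) tests the home programme "against a 70% historical benchmark derived from clinic-based RAT programs, with a pre-specified non-inferiority margin of 5"%. Success requires that "the lower bound of the one-sided 95% confidence interval for the observed utilization rate exceeds 65"%. The analysis is by intention to treat on everyone enrolled, and "participants who withdraw are assigned zero utilization for remaining sessions".

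Section 2.5.1.1 defines the outcome as the percentage of prescribed sessions done, where a day counts if at least 30 minutes of active training are recorded. Section 2.3.2 places daily home training in weeks 1–4 (28 days). Section 2.3 runs the study to week 24.

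**The concern.** The two sections treat the same people in incompatible ways. Under section 2.7, a participant who withdraws partway through home training still has a primary outcome value: the sessions done so far, then zeros. Such a person is not lost to the analysis, so 46 is not the number analysed for the primary outcome. Attrition costs no sample size. It reduces the quantity being tested, and section 2.2.2 does not lower the 70% to allow for that.

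The third part of the dropout definition sharpens the conflict. Completing less than half of the home phase is itself a value of the primary outcome, yet planning sets these people aside as not evaluable.

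What is at stake is the stated power and the meaning of the comparison. This is a single-arm trial judged against one external number, so no concurrent arm would show the same fall from attrition. Whether the 70% includes dropouts affects what the 65% limit means.

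**Working it through.** **Inputs.** Planning and benchmark rate 70%, margin 5 points, N = 54, dropout 15%, one-sided α = 0.10, power 80% (section 2.2.2). Lower one-sided 95% bound above 65%, which is α = 0.05 (section 2.7). The article gives no standard deviation (SD) for utilization and no timing for dropout.

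**Step 1: the plan's own figures.** 54 × 0.85 = 45.9, so the 46 reproduces. The 80% power does not follow from the stated inputs if utilization is treated as a simple proportion. For 65% against 70% at α = 0.10, power = Φ{[(0.70 − 0.65)√n − 1.2816√(0.65 × 0.35)] / √(0.70 × 0.30)}, which is 27.6% at n = 46 and 29.7% at n = 54. For a mean percentage, 80% power needs SD = 5√n / (1.2816 + 0.8416), which is 16.0 points at n = 46 and 17.3 at n = 54. The failure to reproduce the power is a separate matter. Step 4 borrows the implied SD only so that the effect of attrition can be seen from a starting point of 80%.

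**Step 2: expected rate under section 2.7.** Assume 70% among the 85% who continue, and let u be the mean utilization of the 15% who drop out. The rate is 0.85 × 70 + 0.15 × u.

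| Dropouts' pattern | u | Intention-to-treat rate |
|---|---|---|
| No sessions done | 0% | 59.5% |
| Stop halfway on average, at a 70% rate until then | 35% | 64.75% |
| Half the sessions done (upper limit of the under-50% criterion) | 50% | 67.0% |
| All leave after week 4 | 70% | 70.0% |

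Someone who withdraws late in home training with more than half the sessions done falls between the last two rows. The fall from 70% is 10.5 points at u = 0 and 3.0 points at u = 50%, against a 5-point margin. At 10% dropout the range for u = 0 to 50% is 63.0–68.0%.

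**Step 3: what continuers would need.** For an intention-to-treat rate of 70%, continuers must average (70 − 0.15u)/0.85: 82.4% at u = 0, 76.2% at u = 35% and 73.5% at u = 50%.

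**Step 4: power at n = 54.** Power = Φ[(rate − 65)√54 / SD − z], with z = 1.2816 (α = 0.10) or 1.6449 (α = 0.05). Each cell gives α = 0.10, then α = 0.05. The SDs are assumptions.

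| True rate | SD 16 | SD 17.3 | SD 25 | SD 30 |
|---|---|---|---|---|
| 70% | 84.5 / 74.3% | 80.0 / 68.4% | 57.5 / 43.0% | 47.7 / 33.7% |
| 67% | 35.8 / 23.4% | 33.3 / 21.3% | 24.4 / 14.5% | 21.4 / 12.4% |
| 64.75% | 8.1 / 3.9% | 8.3 / 4.0% | 8.8 / 4.3% | 9.0 / 4.4% |

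At 59.5% power is below 1% throughout. Holding the SD fixed is a simplification, since zero-filling would be expected to widen the spread.

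**The case against.** A reader might infer that the 70% benchmark excludes dropouts, so that home and clinic are not compared like with like. The article does not say this. It gives the source only as clinic-based programmes. If the 70% already counts dropouts as zero, a home programme equal to the benchmark sits at 70%, and mixing in a further 15% of low users would count them twice. That stands, and it is why the arithmetic above is conditional.

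A reader might also take 67% as the most that 15% dropout allows. It is not. The under-50% limit belongs to one of three dropout criteria. Withdrawal or loss after week 4 leaves no prescribed home sessions to score zero, so the range extends to 70%. (Table 2 marks H-Man training as continuing at week 6; if prescribed sessions ran past week 4, the exposed period would be longer.) Zero-filling is stated for those who withdraw, not for loss to follow-up, and low use without withdrawal is simply the observed outcome.

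Nor would a shortfall mean that home training is declared inferior. Section 2.7 says only when non-inferiority is shown. The effect runs against the trial's own claim, so it cannot produce a false success. Counting people who stop as non-users is a sound choice for an implementation outcome.

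Sizing on 46 and analysing 54 can be defended as conservative for precision. That is true of precision, but it does nothing about a lower expected rate. The per-protocol sensitivity set does not help either: it requires at least 75% session completion, so every member exceeds 65% by construction.

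**Conclusion.** The point holds as a contradiction between planning and analysis. Section 2.2.2 charges dropout to the sample size, section 2.7 charges it to the rate, and neither the 70% nor the 80% power is adjusted. The size depends on two things that the article leaves open: what the 70% measures and when dropouts leave.

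- If 70% is the rate among those who continue, the expected rate is 59.5–67.0% when dropouts leave during home training having done at most half their sessions, and up to 70% if all leave after week 4. With an SD chosen to give 80% power at 70%, power at 67.0% is about 33% at the planning α and 21% at the section 2.7 bound.
- If 70% already counts dropouts as zero, the benchmark is fair. What remains wrong is the 46-evaluable statement for the primary outcome.

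The documents do not establish that the benchmark is mismatched. They establish that its footing is unstated and that the planning does not match the analysis.

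**What to change.** 1. In section 2.2.2, replace the 46-evaluable basis with n = 54 for the primary outcome. State the assumed intention-to-treat utilization after 15% dropout with zero-filling, including the assumed timing of dropout, and restate the power at that rate.
2. In sections 2.2.2 and 2.7, put the 70% benchmark, and so the 65% limit, on the same footing as the trial figure: all who started, with zero after withdrawal. Say that this is what the two figures mean.
3. If the historical source cannot be re-tabulated that way, describe 65% as a fixed performance goal and do not claim non-inferiority to clinic-based robot-aided therapy.

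This costs protocol wording and one re-tabulation of the historical source, with no added participants or visits. The downside is a less favourable stated power or a more modest conclusion.

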**Methods:**

This pragmatic, single-arm, multi-center prospective trial will recruit 54 adults with subacute to chronic stroke (>28 days post-event) with upper extremity impairment (Fugl-Meyer Assessment 10–60) across three tertiary rehabilitation centers in Singapore. The intervention comprises four weeks of intensive home-based, caregiver-supervised training using the H-Man robot (60–120 min daily) with weekly telemonitoring, combined with four conventional occupational therapy sessions over an eight-week treatment period. The primary outcome is utilization rate (≥75% compliance) measured by cloud-based metrics. Secondary outcomes include motor impairment (FMA-UE), functional capacity (ARAT), quality of life (EQ-5D-5L), usability (System Usability Scale), and technology acceptance, assessed at baseline, 6, 8, 12, and 24 weeks. Economic evaluation will assess cost-effectiveness from healthcare system and societal perspectives.

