#### Phase 3: follow-up (weeks 9–24)

2.3.3

Assessments: week 12 and 24 to evaluate sustainability of gains

All formal outcome assessments (baseline, Week 6, Week 8, Week 12, and Week 24) are conducted in-clinic at the respective study sites by the designated assessor, ensuring standardized testing conditions and access to calibrated equipment (e.g., Jamar dynamometer). The in-clinic setting also facilitates clinical safety review at each assessment timepoint (see Table 2).

**Table 2 tab2:** Intervention schedule and assessment timeline.

Week	0	1–4	6	8	12	24
Phase	Onboarding	Home Training	Mid-Treatment	End-Treatment	Follow-up	Follow-up
H-MAN Training	Training	Daily 60–120 min	Continued	Complete	-	-
Conventional occupational Therapy (COT)	-	2 sessions, fortnightly intervals	1 session	1 session	-	-
Telemonitoring	-	Weekly x4	-	-	-	-
Assessments (total 5)	Baseline	-	Primary	Secondary	Maintenance	Long-term

To ensure consistency and minimize bias, each site designates a primary treating therapist responsible for all enrolled participants at that site, including onboarding, telemonitoring, and conventional therapy sessions. Outcome assessments are conducted by a separate trained assessor at each site who is not involved in treatment delivery, thereby maintaining blinding to treatment progress. All assessors undergo centralized training using standardized assessment protocols and video calibration sessions prior to study commencement, with inter-rater reliability established at >0.85 (ICC) for FMA-UE and ARAT.

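### The FMA-UE mixed model uses the baseline score as both response and covariate under an unstructured covariance, so its likelihood has no maximum; the added random intercept is redundant for all six outcomes

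*Protocol article*

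**What the plan says.** The model is in section 2.7 (Statistical analysis plan) of the protocol article. It covers six outcomes, FMA-UE among them: "For secondary clinical outcomes (FMA-UE, ARAT, grip strength, EQ-5D-5L, SIS-16, PROMIS-10), linear mixed-effects models are employed". The fixed effects, followed by the random effect, are "time (categorical: baseline, Week 6, Week 8, Week 12, Week 24), site, and baseline severity (FMA-UE score), and a random intercept", so the first visit is a level of time and the baseline score is also a regressor. The same sentence gives the random effect in full as "a random intercept for participant to account for within-subject correlation across repeated measures". The next sentence reads: "An unstructured covariance matrix is specified, with model fit compared against compound symmetry using the Akaike Information Criterion".

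Section 2.3.3 lists the same five occasions: "All formal outcome assessments (baseline, Week 6, Week 8, Week 12, and Week 24) are conducted in-clinic". Nothing in section 2.7 exempts FMA-UE from the covariate, removes the baseline row from its response, or makes the random intercept and the unstructured matrix alternatives to each other.

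**The concern.** There are two separate faults.

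1. **FMA-UE only.** A variable that is one of five repeated responses is also a covariate with one common slope. At baseline the response equals the covariate, so slope 1 predicts it perfectly. An unstructured matrix gives baseline its own variance, and nothing stops that variance from going to zero.
2. **All six outcomes.** A participant random intercept adds the same constant to every element of the 5 × 5 covariance matrix. An unstructured matrix can already absorb that constant, and so can compound symmetry.

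At stake is whether the stated FMA-UE analysis can be run, and whether the stated AIC rule can choose between the two structures. If neither works, the covariance model will be chosen with the data in hand. The exploratory subgroup analyses use interaction terms in the same models, so the FMA-UE subgroup models inherit the first fault.

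**Working it through.** There is no figure in the plan to reproduce, since this is a matter of model specification.

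**Inputs from the article.** Five occasions (sections 2.3.3 and 2.7); 54 participants to be recruited (Abstract); a minimum of 46 evaluable (section 2.2.2).

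**Step 1: the likelihood for FMA-UE.** Write B for the baseline score and b for its slope. After the time means are removed, the baseline residual is (1 − b)(B − mean of B), and each later residual is that visit's centred score minus b(B − mean of B). The determinant of the residual covariance matrix is then (1 − b)² × var(B) × a term free of b. With n participants the profile log-likelihood is

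L(b) = L(0) − n ln|1 − b|,

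which has no upper bound as b approaches 1. Each tenfold approach adds n ln 10: 54 × 2.3026 = 124.3, or 46 × 2.3026 = 105.9 with 46 participants. The increment does not depend on the data.

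One simulated data set confirms this (assumed values: n = 54, between-person SD 11, visit error SD 3, response SD 3):

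| Slope b | Log-likelihood | Baseline residual variance |
|---|---|---|
| 0 | −786.2 | 95.9 |
| 0.9 | −661.9 | 0.96 |
| 0.99 | −537.6 | 0.0096 |
| 0.999 | −413.2 | 0.000096 |
| 0.99999 | −164.5 | about 1e−8 |
| 0.9999999 | +84.1 | about 1e−12 |

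The article does not say whether full or restricted likelihood is used. Restricted likelihood does not help. The baseline row determines four fixed effects (intercept, two site terms, slope), so the increment becomes (54 − 4) × 2.3026 = 115.1 per step; a numerical check gave the same value.

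**Step 2: the AIC rule.** Unstructured has 15 covariance parameters and compound symmetry has 2, a penalty difference of 2 × 13 = 26. One tenfold step in the slope lowers the unstructured AIC by 2 × 124.3 = 248.7. Compound symmetry forces a common variance at all visits and so stays bounded. AIC therefore always selects the degenerate fit.

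**Step 3: redundancy of the random intercept.** The marginal covariance has 5 × 6 / 2 = 15 distinct elements.
- Random intercept plus unstructured: 16 parameters, rank 15.
- Random intercept plus compound symmetry: 3 parameters, rank 2.

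In each case one parameter is surplus. The marginal covariance is still identified, and the contrasts and their standard errors depend only on it. If software counts the surplus parameter in one model and not in the other, AIC shifts by 2.

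**Step 4: what happens with a random intercept alone.** The model then fits. In the simulated data set the Week 24 change was 3.926 (SE 0.613) with or without the baseline covariate. Over 150 simulated trials with baseline-dependent dropout, the mean estimates were 4.91 with the covariate and 4.94 without (true value 5).

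**Step 5: standard error under compound symmetry (assumed values only).** Of the ten visit pairs, four involve baseline. If the variance of change is C and the variance of a difference between two post-baseline visits is D, compound symmetry uses 0.4C + 0.6D in place of C. The ratio of model SE to true SE is √(0.4 + 0.6 D/C). The first four rows take baseline SD 13 and visit error SD 2.5, so D = 2 × 2.5² = 12.5 and C = ((1 − slope) × 13)² + (change SD)² + 2.5². The fifth uses the simulation values of step 1, so C = 3² + 2 × 3² = 27 and D = 2 × 3² = 18.

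| Assumption | C | D | SE ratio | Coverage of 95% interval |
|---|---|---|---|---|
| Slope 0.95, change SD 2.5 | 12.9 | 12.5 | 0.99 | 94.8% |
| Slope 0.90, change SD 2.5 | 14.2 | 12.5 | 0.96 | 94.1% |
| Slope 0.95, change SD 3 | 15.7 | 12.5 | 0.94 | 93.4% |
| Slope 0.85, change SD 3.5 | 22.3 | 12.5 | 0.86 | 90.7% |
| Simulation values of step 1 | 27 | 18 | 0.89 | 92.0% |
| D twice C | – | – | 1.26 | 98.7% |

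The error can go in either direction.

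**The case against.** **Severity might enter as a category.** The subgroup paragraph of section 2.7 uses the same term for a split at 30 points. A two-level factor could not make the baseline residuals vanish. But the model sentence specifies the score, and the continuous reading is the natural one.

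**Unstructured might describe the random effects.** With a single intercept that matrix is 1 × 1, and comparing it with compound symmetry would have no content. The residual reading is the only one that gives the AIC comparison meaning.

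**The redundancy is mostly harmless.** This stands. For ARAT, grip strength, EQ-5D-5L, SIS-16 and PROMIS-10 it is the only fault, and it does not alter the contrasts.

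**The harm is limited.** This also stands, and three stronger inferences should be resisted.
- A reader might infer that the trial's main clinical result is lost. The article lists FMA-UE first among six secondary outcomes but does not rank it, and the primary outcome is utilization.
- A reader might infer that a failed fit would be repaired after unblinding. The trial is single-arm, so there is no allocation to unblind, and compound symmetry is already named as the comparator.
- A reader might infer that the fallback understates standard errors by a fixed amount, such as 14% (ratio 0.86). That is one assumed covariance. It measures compound symmetry rather than the duplicated baseline, and the documents give no figure to support it.

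**Conclusion.** The specification is wrong as written, within limits. For FMA-UE, the stated combination of baseline as a time level, baseline score as covariate and unstructured covariance has no maximum likelihood, and the AIC comparison is meaningless. This follows algebraically and needs no assumed values. It rests only on the two readings above: a continuous covariate and an unstructured residual matrix.

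For all six outcomes the random intercept is redundant. The consequence is possible convergence trouble and miscounted AIC parameters, not wrong estimates. A compound-symmetry or random-intercept fallback does fit, and its estimates of change are essentially unaffected by the covariate. Its standard errors may be too small or too large, depending on a covariance that the documents do not give. The primary utilization analysis does not use this model.

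**What to change.** Amend section 2.7, or the corresponding text of the full analysis plan, as follows:

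- For FMA-UE, keep baseline as a level of time and remove the baseline FMA-UE covariate. The covariate may stay in the other five models. The same change cures the FMA-UE subgroup models.
- Where the unstructured residual matrix is used, drop the random intercept. That leaves 15 parameters for 15 elements.
- State compound symmetry, or a random intercept alone, as the fallback if the unstructured fit does not converge. Quote any resulting error in the standard errors only as a range under stated assumptions.

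If the team prefers to model only Weeks 6 to 24 with centred baseline as a covariate, the degeneracy also goes, but the standard error of mean change from baseline must then include sampling variation in the baseline mean. On the assumed values of slope 0.85, change SD 3.5, visit error SD 2.5 and baseline SD 13, the model SE is √(18.5/54) = 0.585, where 18.5 = 3.5² + 2.5². The true value is √(22.3/54) = 0.643. The model SE is about 9% too small, with coverage near 93%.

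The cost is wording only, with no new data or participants.

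### Letting AIC choose between only unstructured covariance and compound symmetry can leave Week 24 intervals for the secondary outcomes modestly too narrow

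*Protocol article*

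**What the plan says.** Section 2.7 of the protocol article fits linear mixed models to six secondary outcomes: FMA-UE, ARAT, grip strength, EQ-5D-5L, SIS-16 and PROMIS-10. Fixed effects are time (five categorical visits), site and baseline FMA-UE. The model also has "a random intercept for participant to account for within-subject correlation across repeated measures". On the covariance it states: "An unstructured covariance matrix is specified, with model fit compared against compound symmetry using the Akaike Information Criterion". No third structure and no robust standard error is named.

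Section 2.3.3 gives the purpose of the late visits as "week 12 and 24 to evaluate sustainability of gains". Section 2.2.2 sets enrolment at 54 and adds: "This sample accounts for an anticipated 15% dropout rate (approximately 8 participants), yielding a minimum evaluable sample of 46 participants".

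**The concern.** Gaps between visits run from 2 weeks (Week 6 to 8) to 24 weeks (baseline to Week 24). Compound symmetry forces one correlation on all of them, whereas repeated clinical measurements usually correlate less the further apart they are. The only alternative to the unstructured matrix is therefore a structure that the visit spacing makes doubtful. With about 50 participants, AIC's charge for 13 extra parameters is large compared with the evidence that moderate decay can supply.

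If compound symmetry is kept when correlation decays, every pair of visits gets the same standard error. It is then too small for long gaps and too large for short ones. In a single-arm trial the within-participant change is the main quantity these models estimate. P-values that are too small for Week 24 would enter the Benjamini-Hochberg procedure, which cannot repair them.

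**Working it through.** **Inputs.** Visits are at Weeks 0, 6, 8, 12 and 24 (2.7). Sample size is 54 enrolled with 15% dropout (2.2.2): 54 × 0.85 = 45.9, which reproduces the stated 46 evaluable. Whether 54 gives the stated power for the primary outcome is a separate question and is not used here. The protocol gives no correlations, standard deviations or selection frequency, so everything on correlations below is an assumption shown as a range.

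**Step 1: the AIC hurdle.** AIC = −2 log L + 2k. Unstructured: k = 5 × 6 / 2 = 15. Compound symmetry: k = 2. The penalty gap is 2 × (15 − 2) = 26, so compound symmetry wins whenever the likelihood-ratio statistic is below 26.

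**Step 2: direction and size of the distortion.** With equal SDs, the standard error of a change between visits i and j is σ√(2(1 − ρᵢⱼ)/n). Compound symmetry in effect replaces ρᵢⱼ by the average correlation. The ten pairwise gaps (6, 8, 12, 24, 2, 6, 18, 4, 16, 12 weeks) sum to 108, mean 10.8. If correlation falls linearly from a at 2 weeks to b at 24 weeks, the average is a − (a − b)(10.8 − 2)/22 = a − 0.4(a − b).

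Example, 0.90 falling to 0.80: the average is 0.86.
- Baseline to Week 24: √(0.14/0.20) = 0.84, so the standard error is 16% too small.
- Baseline to Week 6: ρ = 0.90 − 0.10 × 4/22 = 0.882; √(0.14/0.118) = 1.09, so 9% too large.
- Week 6 to Week 8: √(0.14/0.10) = 1.18, so 18% too large.

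**Step 3: how often AIC keeps the false structure** (simulation, n = 54, 2,000 trials per scenario).

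| Correlation, 2-week to 24-week gap | Week 24 SE, compound symmetry ÷ true | Compound symmetry chosen |
|---|---|---|
| 0.90 to 0.85 | √(0.12/0.15) = 0.89 | 89% |
| 0.60 to 0.40 | √(0.48/0.60) = 0.89 | 87% |
| 0.90 to 0.80 | √(0.14/0.20) = 0.84 | 61% |
| 0.80 to 0.60 | √(0.28/0.40) = 0.84 | 58% |
| 0.90 to 0.75 | √(0.16/0.25) = 0.80 | 32% |
| 0.80 to 0.50 | √(0.32/0.50) = 0.80 | 29% |
| 0.90 to 0.70 | √(0.18/0.30) = 0.77 | 14% |

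It falls to 1% for 0.95 to 0.80, and to 0% for serial decay without measurement error. Over 22 scenarios in which compound symmetry is false, the range is 0–89% at n = 54 and 0–90% at n = 46. It was chosen more than half the time in 9 of the 22.

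**Step 4: coverage of nominal 95% intervals, baseline to Week 24.**
- Decaying correlation, compound symmetry usually chosen: about 91–94% after selection.
- Compound symmetry badly wrong (Week 24 SE 20–31% too small): it would cover 81–89% if always used. AIC chooses it in only 0–32% of trials (0–43% at n = 46), and coverage after selection is 92–95%.
- Unstructured always kept: 94–96%.

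A second simulation used a participant effect plus exponential serial correlation plus noise, with correlations of 0.65–0.88 at 2 weeks and 0.44–0.77 at 24 weeks. At n = 54, compound symmetry was chosen in 35–82% of trials; Week 24 coverage was 92.6–93.6% and Week 6–8 coverage 96.2–97.2%. At n = 46 it was chosen in 45–85%, with Week 24 coverage of 92.0–93.4%. Keeping unstructured gave 94.5–95.7%.

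**Step 5: closer to the planned model** (site and a baseline covariate in the mean, 15% monotone dropout, 300 trials per scenario). For 0.90 to 0.80, 0.80 to 0.60, 0.90 to 0.75 and 0.90 to 0.70, compound symmetry was chosen in 65%, 67%, 44% and 20% of trials. If baseline FMA-UE correlates 0.8 with the baseline outcome, these fall to 40%, 24%, 14% and 7%.

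**The case against.** A reader might infer that AIC will usually pick a false compound symmetry in this trial. The documents do not support that. The frequency depends on correlations they do not give, it exceeded one half in only 9 of 22 scenarios, and it dropped below one half throughout when baseline FMA-UE strongly predicted the outcome. The problem also partly limits itself, since AIC mostly retains the unstructured matrix when compound symmetry is badly wrong. All of this stands.

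Section 2.7 names the unstructured matrix first and never says that the AIC winner replaces it. That is correct as to the wording, but a fit comparison has little purpose unless the better-fitting structure is used, so replacement is the natural reading.

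Comparing structures by AIC is common practice, and convergence rules and fallbacks often sit in a full analysis plan. An absent fallback is therefore no fault here. The point rests on the two-candidate rule that is stated.

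A reader might also take baseline to Week 24 as the designated test of durability. The protocol does not say so: its sustainability aim could equally mean Week 8 to Week 24, and Table 2 marks Week 6 as the primary assessment.

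Finally, FMA-UE at baseline is both an outcome row and a covariate. The unstructured likelihood can then be degenerate and AIC uninformative, so the simulations do not describe that outcome.

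**Conclusion.** The point holds in a conditional form, and it is minor. With five unequally spaced visits and 46–54 participants, the stated rule can keep a false compound symmetry under mild to moderate decay of correlation. Where that happens often, the error rate for baseline-to-Week 24 change is about 6–9% instead of 5% (100 − 94 to 100 − 91), and short-gap intervals are somewhat conservative. Under steep decay the rule does little harm.

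This rests on assumed correlations, on the AIC winner being the structure used, and on roughly stable SDs. With constant correlation and only rising SDs, the Week 24 standard error is just 3–5% too small. Only secondary outcomes are touched; the utilization analysis does not use these models.

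**What to change.** In section 2.7, delete the AIC comparison and the random intercept, and state:

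> An unstructured within-participant covariance matrix is used regardless of AIC, with no additional random intercept. If the model does not converge, a heterogeneous structure with correlation decaying in the actual time between visits is used, or compound symmetry with small-sample-corrected robust standard errors.

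The random intercept has to go because its variance cannot be separated from an unstructured residual matrix; the two together are over-parameterised. Alone, a random intercept already implies compound symmetry. For FMA-UE, the double use of baseline as outcome and covariate needs to be settled as well, or the unstructured fit may fail for that outcome.

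The cost is one sentence in the plan and slightly wider Week 24 intervals. Sample size, data collection and the primary analysis do not change.
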